**Figure 2 fig2:**
[figure not shown]
JUSTICE Study Design. A single-center, randomized, double-blind, placebo-controlled, pilot phase 2 trial of baricitinib in patients with proteinuria, APOL1-associated FSGS or APOL1-associated, hypertension-attributed CKD without diabetes. Following CARE screening (Visit 1), JUSTICE screening (visit 2) requires in-person visit and includes collection of blood sample. Participants will have the option of virtual visits for study visits 3 to 9.

### End Points

The primary efficacy end point is percent change in UACR from baseline to end of month 6. Because anemia is a relevant potential adverse effect of baricitinib for which patients with CKD may be more vulnerable, the primary safety end point is incidence of a clinically significant decrease in hemoglobin of ≥1 g/dl. We will measure UACR at baseline and at the end of each of the 6 months for a total of 7 assessments. We will also assess eGFR at baseline and monthly as a secondary safety measure. Because of the known effect of baricitinib to reduce tubular secretion of creatinine^28^ we will measure eGFR using the CKD-Epidemiology Collaboration Cystatin C equation^35^ rather than a creatinine-based equation. As an exploratory analysis of target engagement by baricitinib, we will also measure the chemokine biomarker, urine CXCL9-11, with standard assays at baseline and at each study visit.

### Statistical Analyses

We will use standard descriptive statistics to compare clinical characteristics at baseline according to the treatment arm. The primary analysis will be a comparison of differences in percent change in UACR from baseline to month 6 across treatment arms in the overall study population using 2-sample t-tests. This primary analysis will be conducted according to the intention-to-treat principle with participants analyzed according to the treatment arm to which they were randomized, regardless of subsequent crossover or post-randomization treatment. In secondary analyses, we will compare the effects of baricitinib versus placebo on percent change in UACR within each of the APOL1 disease strata (FSGS and HTN) separately. In further analyses, we will assess the between-group and within-group changes in UACR using linear mixed models with visit number (baseline, months 1–6) representing the repeated-measures factor and randomization arm treated as a fixed-effect term. We will select the appropriate covariance matrix (e.g., compound symmetry, autoregressive, unstructured, etc.) based on the data to account for repeated observations. The statistical test for significant differences between the groups will be the time x group interaction that assesses the overall differences between groups in longitudinal UACR. The mixed model analyses will enable us to assess within subject changes in UACR over time, and to adjust for any imbalances in baseline factors that may occur in this relatively small study. We will use the same strategy involving linear mixed models to assess the effects of the intervention on eGFR and the chemokine biomarkers (CXCL9–11). For the primary assessment of safety, we will investigate the incidence of hemoglobin reduction by ≥1 g/dl in each arm and the mean change in hemoglobin from baseline to the end of study in each arm. We will also report adherence based on pill count data and use standardized methods to report all adverse events.

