### Sample Size and Power Calculation

In Table 4, we present sample size estimates, assuming 30%, 35%, and 40% differences between baricitinib and placebo, power of 80% or 85%, different SDs for percent change in UACR from baseline to the end of month 6, and the 2:1 active:placebo randomization scheme. For the purpose of the power calculation, we assumed 0% change in UACR in the placebo arm. Assuming the higher SD of 50%, a sample of 75 participants (50 in treatment arm and 25 in placebo arm) will provide 80% power to detect a 35% decrease in UACR at month 6 compared to placebo in the overall study population with a 2-sided significance level of 5%. A total of 25 patients with FSGS and 50 patients with HTN-associated CKD will be enrolled into the study. There will be no planned interim analyses although the Data Safety and Monitoring Board will have access to unblinded results at their regularly scheduled meetings. Approval of the study design and procedures was obtained from the Duke University Institutional Review Board before enrollment. Written informed consent is obtained for participation in the study.

**Table 4 tbl4:** Sample size and power calculation

Standard deviation	Difference	Power	Required Sample size		
			Total	Baricitinib	Placebo
SD = 0.33	0.30	80%	45	30	15
		85%	51	34	17
	0.35	80%	36	24	12
		85%	39	26	13
	0.4	80%	27	18	9
		85%	30	20	10
SD = 0.50	0.30	80%	102	68	34
		85%	117	78	39
	0.35	80%	75	50	25
		85%	87	58	29
	0.4	80%	60	40	20
		85%	66	44	22

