### Randomization and Intervention

The study design is illustrated in Figure 1. Participants will be required to be on standard-of-care, including a stable dose of angiotensin-converting enzyme inhibitors or angiotensin 2 receptor blocker for at least 30 days before randomization. Participants must have systolic blood pressure less than 180 mm Hg or diastolic blood pressure less than 90 mm Hg prior to randomization. Duke Pharmacy Investigational Drug Services will randomly assign participants 2:1 to baricitinib or placebo. According to this schema, 17 participants with FSGS will be randomized to baricitinib and 8 to placebo. Among patients with HTN-CKD, 33 will be randomized to baricitinib and 17 to placebo. We opted for this 2:1 randomization to maximize the number of patients treated with baricitinib who will support within group analyses of change in UACR over time. Baricitinib will be dose-adjusted for eGFR: 1 mg once daily orally for eGFR of 30 to 50 ml/min per 1.73 m^2^; 2 mg once daily orally for eGFR > 50 ml/min per 1.73 m^2^. The duration of treatment will be 6 months.

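### The primary t-test leaves out baseline UACR and disease group; prespecified adjustment would cost almost nothing, though the documents do not allow its gain to be sized

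*Protocol article*

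**What the plan says.** End Points defines the outcome: "The primary efficacy end point is percent change in UACR from baseline to end of month 6". Statistical Analyses fixes the primary test as a comparison "across treatment arms in the overall study population using 2-sample t-tests", by intention to treat, with no covariate or stratification term.

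Two baseline variables are available by design:

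- Data Collection defines baseline UACR as the average of two first morning voids at least two days apart.
- Randomization and Intervention states the split by disease group: "17 participants with FSGS will be randomized to baricitinib and 8 to placebo", and 33 to 17 in HTN-CKD. Statistical Analyses calls these groups disease strata.

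Disease group enters only secondary comparisons made within each group. Adjustment for baseline appears only in the further linear mixed models, which are said to make it possible "to adjust for any imbalances in baseline factors that may occur in this relatively small study".

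**The concern.** Change from baseline usually still depends on the baseline value, and dividing by baseline to form a percent change does not in general remove that dependence. Whatever part of the within-arm variance baseline UACR explains stays in the error term of an unadjusted test.

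Disease group raises a second point. When allocation balances a factor that affects outcome, the treatment estimate does not carry the between-group variation, but the ordinary t-test still counts that variation in its standard error. The test is then conservative.

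At stake is the width of the confidence interval and the chance of detecting an effect in a trial with 25 placebo patients. The sample size is exactly the Table 4 requirement for 80% power, so there is little slack.

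**Working it through.** **Inputs from Sample Size and Power Calculation.** SD of percent change 0.50, difference 0.35 (placebo change taken as 0), two-sided 5% level, 50 v 25 patients. The plan's claim is that this sample "will provide 80% power to detect a 35% decrease in UACR at month 6 compared to placebo".

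**Step 1: the plan's own figure.** The standard error is 0.50 × √(1/50 + 1/25) = 0.50 × 0.2449 = 0.1225. The noncentrality is 0.35/0.1225 = 2.86. With 73 degrees of freedom, the noncentral t gives power of 80.5%. The same method reproduces all 12 rows of Table 4. The sample size therefore rests on the unadjusted t-test and takes no credit for covariates.

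**Step 2: adjusted power.** Let R² be the share of within-arm variance of percent change explained by baseline UACR and disease group together. The residual SD is 0.50 × √(1 − R²), with 75 − 4 = 71 degrees of freedom. The documents give no R², so these values are assumptions:

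| R² (assumed) | Residual SD | Power at N = 75 | 95% CI half-width (points) |
|---|---|---|---|
| 0 | 0.500 | 80.5% | 24.4 |
| 0.05 | 0.487 | 82.4% | 23.8 |
| 0.10 | 0.474 | 84.4% | 23.2 |
| 0.20 | 0.447 | 88.3% | 21.8 |

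At R² = 0 power is 80.48% on 71 degrees of freedom against 80.51% on 73. That is the whole cost.

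**Step 3: what disease group alone can contribute.** One third of patients have FSGS. A difference d between the groups in mean percent change gives R² = (1/3)(2/3)d²/0.25:

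- d = 0.10: R² = 0.009
- d = 0.30: R² = 0.08
- d = 0.50: R² = 0.22

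Disease group adds little unless the two conditions run very different courses.

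**Step 4: the standard error under the stated split.** Trials were simulated with 17:8 and 33:17 allocation, total within-arm SD 0.50 and 10,000 runs per scenario. With a 30-point difference between disease groups, the unadjusted test rejected a true null in 4.3% to 4.4% of runs. With a 50-point difference it did so in 2.7%. The adjusted model stayed at 4.9% to 5.1%. The unadjusted test thus errs on the safe side and gives up precision in doing so.

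**The case against.** The strongest reply is that nothing here is stated wrongly. Randomization makes the t-test valid, the sample size was computed for that test, the two agree, and the document calls itself a pilot phase 2 trial. All of that stands. The point is about efficiency.

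Four stronger readings are tempting, and the documents do not support them.

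- **Disease imbalance could bias the result.** Under the stated split FSGS makes up 17/50 = 34% of the baricitinib arm and 8/25 = 32% of placebo, so no material imbalance can arise. The article does not use the term stratified randomization, but its per-group counts and its word strata support this reading.
- **Adjustment would bring a definite gain of 4 to 8 points of power.** On the log scale with equal variances at both times, the ratio of adjusted to change-score variance is (1 + ρ)/2. That is 0.80, 0.85 and 0.90 for assumed correlations of 0.6, 0.7 and 0.8, and would suggest power of 88%, 86% and 84%. But this applies a log-scale ratio to an SD and a difference defined for percent change. It also needs equal variances, which the entry threshold of 300 mg/g at screening makes doubtful. With baseline SD assumed to be 0.8 of month-6 SD, the ratio is (1 − ρ²)/(1 + 0.64 − 1.6ρ) = 0.94, 0.98 and 1.00, and power is 82.8%, 81.2% and 80.5%.
- **Covariates will be chosen after seeing the data.** The remark on imbalances concerns the further mixed models, not the primary test, and says what those models allow. Their covariate list can properly be left to an analysis plan that is not shown.
- **Adjustment is needed to rescue power after dropout.** The sample size section states no dropout rate, so any evaluable number below 75 would be the reader's own assumption.

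**Conclusion.** The point holds as a missed gain in precision, not as an error of validity. The primary t-test is valid and delivers its stated power. It leaves out two variables that the design already provides, and it is conservative if FSGS and HTN-CKD differ in course.

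The documents do not determine the size of the gain. It is nil if the covariates explain nothing, about 4 points of power at an assumed R² of 10%, and about 8 points at 20%. These figures rest on the plan's SD of 0.50 and difference of 0.35, all 75 patients evaluable, and a linear model with common residual variance. Because the possible loss is under 0.1 point, the change is worth making even though its benefit is uncertain.

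**What to change.** Prespecify the primary comparison as a linear model for percent change in UACR at month 6 with treatment arm, baseline UACR (log-transformed as a covariate) and disease group (FSGS or HTN-CKD). Keep the two-sample t-test as a supportive analysis. Make the change before unblinding.

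This keeps the endpoint and the effect measure, a difference in mean percent change, so Table 4 still applies as a calculation without credit for covariates. The cost is wording and two degrees of freedom; no new data, visits or patients are needed.

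Modelling month-6 UACR itself on the log scale is a separate choice that adjustment does not require. If it is made, the plan should state that the treatment effect becomes a ratio of geometric means and restate the Table 4 inputs on that scale. A 35% reduction in the geometric mean, for example, is a log difference of −ln(0.65) = 0.43, and the article gives no log-scale SD.

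### The mixed models are said to adjust for chance baseline imbalance, but the named time x group test does not do so without terms the article does not state

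*Protocol article*

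**What the plan says.** All of this is in the Protocol article; the full protocol and SAP are not shown.

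- **Primary analysis** (Statistical Analyses): an unadjusted comparison of "percent change in UACR from baseline to month 6 across treatment arms in the overall study population using 2-sample t-tests".
- **Further analyses** (same section): "linear mixed models with visit number (baseline, months 1–6) representing the repeated-measures factor and randomization arm treated as a fixed-effect term". The End Points section confirms seven UACR occasions, of which baseline is one.
- **Covariance** (same section): "We will select the appropriate covariance matrix (e.g., compound symmetry, autoregressive, unstructured, etc.) based on the data".
- **Named test** (same section): "The statistical test for significant differences between the groups will be the time x group interaction".
- **Stated purpose** (same section): the models are to let the investigators "to adjust for any imbalances in baseline factors that may occur in this relatively small study".
- **Reach** (same section): "We will use the same strategy involving linear mixed models to assess the effects of the intervention on eGFR and the chemokine biomarkers".

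The section names no baseline covariate, no covariate-by-visit term, no common-baseline constraint, and no model of follow-up visits with the baseline value as covariate.

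**The concern.** The primary test is unadjusted, so the sentence on the mixed models is the article's only explicit provision for adjusting for chance imbalance in a trial of 50 v 25. The article commits to a model layout, a test and a purpose, and as laid out the test does not serve the purpose.

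An analyst who follows the text in the ordinary way would add, say, baseline eGFR as a fixed effect and report the time x group result as adjusted. That estimate would be the same, or almost the same, as the unadjusted one. A chance difference between arms in baseline UACR would also stay in the contrast.

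The same approach is the only stated treatment-effect analysis for eGFR (a secondary safety measure in End Points) and for CXCL9-11 (exploratory target engagement).

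**Working it through.** **1. The plan's own figure.** Inputs from Sample Size and Power Calculation: difference 0.35, SD 0.50, 50 v 25, two-sided 5%.

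- Noncentrality = 0.35 / (0.50 x sqrt(1/50 + 1/25)) = 0.35 / 0.1225 = 2.858, with 73 degrees of freedom.
- Power from the noncentral t distribution is 0.805, so N = 75 reproduces. It belongs to the t-test, and nothing below changes it.

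**2. What the named test estimates.** Let each arm g and visit t have its own mean, and add a baseline factor x as a main effect with coefficient c. With complete data the fitted mean is

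fitted(g,t) = ybar(g,t) - c x xbar(g).

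The change from baseline in arm g is then

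fitted(g,6) - fitted(g,0) = ybar(g,6) - ybar(g,0).

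The term c x xbar(g) cancels whatever c, the imbalance or the covariance matrix may be. The month-6 interaction term is the raw between-arm difference in mean change. With visit categorical, the overall test is a joint test of (7-1) x (2-1) = 6 such contrasts. If time were linear, a slope x group term would be unaffected in the same way.

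**3. Numerical check.** Simulated data: 50 v 25, seven visits, a prognostic covariate shifted by 0.5 SD between arms with an effect that grows over visits. Each column is a separate simulated data set. Entries are the month-6 arm x visit estimate (SE).

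| Model | Complete, unstructured | Complete, compound symmetry | About 20% dropout, unstructured | About 20% dropout, compound symmetry |
|---|---|---|---|---|
| No covariate | -0.28372 (0.15434) | -0.05965 (0.17575) | -0.53969 (0.18141) | -0.40490 (0.17608) |
| Covariate main effect | -0.28372 (0.15434) | -0.05965 (0.17575) | -0.55371 (0.18209) | -0.40556 (0.17613) |
| Covariate x visit | -0.37935 (0.15749) | -0.18807 (0.19211) | -0.53384 (0.16762) | -0.44518 (0.17758) |
| Common baseline, no covariate | -0.26000 (0.15083) | 0.04392 (0.16670) | -0.57240 (0.17908) | -0.32458 (0.16635) |

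With complete data the raw differences in change were -0.28372 and -0.05965, equal to the first two rows. The 6-df Wald statistic was also identical with and without the main effect (7.449 unstructured, 5.357 compound symmetry). With dropout the main effect moved the estimate by 0.014 and 0.001.

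**4. Imbalance in the outcome's own baseline.** Assume equal variances and a baseline-to-follow-up correlation rho, which the article does not give. A chance baseline difference d shifts the change contrast by -(1-rho) x d:

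- rho 0.5: -0.5d
- rho 0.7: -0.3d
- rho 0.8: -0.2d

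As a cross-check, in the complete compound-symmetry data set d was 0.510. The common-baseline constraint moved the estimate by 0.04392 - (-0.05965) = 0.104, which is 0.20 x 0.510.

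**5. Precision.** For a simple difference with common variance s², the change score has variance 2s²(1-rho) and the baseline-adjusted outcome s²(1-rho²). The ratio is 2/(1+rho):

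- rho 0.5: 2/1.5 = 1.33
- rho 0.7: 2/1.7 = 1.18
- rho 0.8: 2/1.8 = 1.11
- rho 0.9: 2/1.9 = 1.05

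**The case against.** **The article does not say how covariates enter.** A factor-by-visit term or a common-baseline constraint would be compatible with its wording, mixed models can adjust for baseline factors, and such detail often sits in an SAP. This stands in part: a missing covariate list would be no finding. But the article does fix the layout, the test and the aim, and the ordinary reading of the first two does not deliver the third.

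**The result is not exact in every case.** This stands. Exact equality needs complete data and main-effect entry. Also, if an autoregressive covariance is re-estimated after the covariate is added, the estimate stays put but its SE can move (0.329 to 0.300 in one complete-data fit), so a p-value may change although the imbalance is still not corrected.

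**Disease is already handled.** Randomization and Intervention plans 17 v 8 with FSGS and 33 v 17 with HTN-CKD. If that holds, FSGS makes up 17/50 = 34% and 8/25 = 32% of the arms, and UACR is also to be compared within each disease. This lowers the risk for that one factor. It does nothing for baseline UACR, eGFR or other factors.

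**Stronger readings that the documents do not support.**

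- *That the contrast is biased.* Under randomisation it is not, and a change score does subtract the baseline level. The issue is the imbalance that happens in this sample, and efficiency.
- *That a stated number of power points is lost.* The only design inputs are for percent change in the t-test, not the overall time x group test, and no rho is given. UACR entry is at 300 mg/g or above with no stated upper limit. A wide baseline spread would suggest a high rho and a small gain.
- *That choosing covariates from observed imbalance inflates false positives.* The article states no threshold or rule, so no error rate can be attached. If factors enter only as main effects, the choice hardly moves the tested estimate.

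**Conclusion.** The point holds as a defect in how the further analyses are fixed. With baseline among the outcome visits, the time x group test compares change from baseline between arms. It does not adjust for the baseline value of the outcome, and main-effect covariates leave its estimate unchanged with complete data and nearly so with dropout (shifts of 0.014 and 0.001 in the two simulated sets). The stated aim is met only by terms the article does not mention.

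The size is moderate at most. The variance penalty runs from 1.33 at rho 0.5 to 1.05 at rho 0.9, for a simple difference with equal variances and an assumed rho. The primary test and the sample size are not touched, and the analyses concerned are further, secondary or exploratory. It is still worth correcting, because the article relies on these models for adjustment and an agreeing adjusted result could be misread as evidence of robustness.

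**What to change.** Replace the open-ended sentence on adjustment with a fixed specification for the UACR, eGFR and CXCL9-11 mixed models:

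1. Either constrain the two arms to a common baseline mean with arm-by-visit terms from month 1 on, or use months 1 to 6 as the outcome with baseline value x visit as covariate.
2. Include disease group (FSGS or HTN-CKD) x visit in every model.
3. Prespecify any other baseline factor, at most one or two (for example baseline eGFR), and enter each with its visit interaction.
4. Take the treatment contrasts, including month 6, from the arm-by-visit terms of that model.
5. Keep the baseline table descriptive and do not choose covariates from it.

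The cost is wording, with no new data or patients. The downside is a few degrees of freedom: a single-coefficient factor entered by visit takes seven mean parameters in the common-baseline model, or six when only months 1 to 6 are modelled. With 75 participants that is a reason to keep the list short. The investigators also give up choosing covariates after seeing the arms.

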## Discussion

Although African Americans with high-risk APOL1 genotypes have the highest risk of developing idiopathic FSGS and HTN-attributed ESKD,^3^^,^^4^^,^^9^ they are underrepresented in clinical trials of therapeutic agents.^36^^,^^37^ Therefore, there is an urgent unmet need for novel therapies for AMKD. The JUSTICE study is designed to address this unmet need by testing the antiproteinuric efficacy and safety of baricitinib in individuals with AMKD. Preclinical studies demonstrate that the JAK-STAT signaling pathway is the key upstream inducer of APOL1 expression in podocytes and glomerular endothelial cells.^21^^,^^22^ In mouse models, expression of G1 or G2 APOL1 variants in podocytes causes podocyte injury, proteinuria, and kidney injury.^6^^,^^8^^,^^38^ Baricitinib inhibits JAK1/2 and thereby blocks APOL1 expression in podocytes and other kidney cells. JUSTICE is designed to test whether the inhibition of renal APOL1 expression by baricitinib would reduce APOL1-mediated podocyte injury as manifested by proteinuria.

To assess the effect of baricitinib on halting APOL1-induced podocytopathy and glomerulopathy, JUSTICE will compare UACR at the end of 6 month of baricitinib or placebo with baseline proteinuria. We predict that inhibiting expression of pathogenic APOL1 proteins in podocytes will attenuate APOL1-mediated podocyte injury and thereby improve UACR. The use of changes in proteinuria rather than changes in glomerular filtration rate as the primary end point of JUSTICE is due to practical considerations. Treatment-induced improvement in proteinuria is detectable within 6 months. In contrast, longer durations are required for significant changes in glomerular filtration rate to emerge. Nonetheless, changes in eGFR will be measured as an exploratory end point in JUSTICE. The well-established role of podocyte injury and the associated proteinuria as early and frequent phenotypes of AMKD further justifies the use of proteinuria reduction as the primary end point. Detection of a clinically meaningful proteinuria reduction by baricitinib in JUSTICE would provide a strong basis for a longer phase 3 clinical trial in which changes in kidney function would be the primary end point.

It would be ideal to make the stable use of sodium-glucose cotransporter-2-inhibitors (SGLT-2is) at baseline a precondition for enrolment because SGLT-2is reduce kidney disease progression and mortality in patients with CKD, regardless of diabetes status.^39^ However, a recent cross-sectional registry analysis of 49,587 nondiabetic patients with CKD in a large integrated health care system in the US, reported that only a paltry 0.3% of these patients were prescribed SGLT-2i.^40^ Therefore, the current low rate of SGLT-2i prescription in the nondiabetic CKD population would constitute a significant, additional barrier to enrolment of otherwise eligible patients into the JUSTICE trial. Moreover, it is not known that SGLT-2is specifically reduce the rate of progression of AMKD. For these reasons, we did not require the stable use of SGLT-2i as a precondition for enrolment in JUSTICE trial.

To assess the safety of baricitinib in patients with AMKD, we will compare the incidence of anemia a potential adverse effect of JAK-inhibitors in the baricitinib versus placebo recipients. Previous trials in which baricitinib was used in patients with diabetic kidney disease did not show increased incidence of anemia, leucopenia, or thrombocytopenia in participants who received baricitinib versus placebo.^28^ Based on this precedent, our expectation is that baricitinib will also be well-tolerated in JUSTICE.

A unique feature of JUSTICE is the active engagement of African Americans/Black individuals both in the community and in clinical settings for study recruitment. A similar community-engaging strategy is being effectively employed by the ongoing National Institutes of Health–funded APOL1 Long-term Kidney Transplantation Outcomes Network (APOLLO) (NCT03615235).^41^ Through the CARE registry, JUSTICE investigators will work with a well-established network of regional and national community partners who are trusted leaders, connectors, and influencers in the broader African American community. These partners are committed to advancing health equity and addressing racial health disparities. This includes leadership of religious, educational, civic, and social organizations. The CARE registry provides accessible information about the high burden of CKD, especially ESKD, and the causal role of APOL1 HRGs. Test results are returned to all participants who express desire to receive them. Genetic counseling is offered to interested participants. This bidirectional community engagement and screening activity will help to increase awareness and access to trustworthy kidney disease information, screening, and clinical research with the goal of reducing the longstanding trust deficit between the African American community and biomedical research organizations. It also increases the opportunity for identifying individuals with APOL1 HRG who have proteinuric kidney disease, not due to diabetes, that could be further screened for participation in JUSTICE study.

The combined strategy of community engagement and mechanism-informed therapeutic trial could serve as a model for future trials aimed at African Americans and other ethnic groups who are underrepresented in clinical trials.
